#### **9.4.3 ANALYSIS OF THE SECONDARY EFFICACY HYPOTHESES**

The one-sided proportion test will be conducted for DCR against the null hypothesis that the DCR is less than or equal to 45%, with significance level of 0.05. The cumulative frequency, estimated proportion, and the exact 95% confidence intervals will be reported. A sample size of 48 achieves 87% power if the DCR is 65% using a one-sided exact test with a target significance level of 0.05. These results assume that the DCR of the historical control is 45%.

The one-sided, one sample log rank test will be conducted for PFS against the null hypothesis assuming that the hazard ratio of progression to the historical control is 1 while assuming the progression free survival probability at 6 months of the historical control is 20%. The survival probability (Kaplan-Meier survival curve) at 6 months will be calculated by the Kaplan-Meier method; the survival curve and the median survival time will be reported with the corresponding 2-sided 95% Brookmeyer-Crowley's Confidence Interval if feasible. A one-sided, one-sample log-rank test calculated from a sample of 48 subjects achieves 95.6% power at a 0.05 significance level to detect a 6-month progression free survival probability of 40% in the treatment group when the 6-month progression free probability in the historic control group is 20%. Assuming that subjects are accrued for 1 year and follow-up continues for 6 months after the last subject is added, the probability that a subject progress during the study is 0.82. The expected number of progression events during the study is 39. It is assumed that the survival time distributions of both groups are approximated reasonably well by the Weibull distribution with a shape parameter of 1.

DOR power calculations were not performed and DOR was not used to determine sample size. DOR will be compared to historical controls if sample size allows.

OS power calculations were not performed and OS was not used to determine sample size. OS will be compared to historical controls if sample size allows.

---

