## Footnotes

1. Screening: to be obtained within 28 days prior to study entry (ie: prior to C1D1).
2. Informed Consent: must be obtained prior to undergoing any study specific procedures.
3. Tumor History: History of CRC should include stage, date of first diagnosis, site of primary disease, previous biopsies particularly date and site of biopsy, location of metastases, previous treatments administered including all surgeries and radiation therapy, previous clinical trials especially details of any previous use of immunotherapies, ECOG performance status, MMR/MSI status, tumor mutational burden (TMB), and mutational testing particularly KRAS, NRAS, and BRAF.
4. Demographic/Medical History: Includes age, sex, self-reported ethnicity, detailed description of history of non-CRC cancer, past medical and surgical history, list of medications including prescription, OTC, herbal, homeopathic, nutritional drugs, performance status, social history including alcohol, tobacco and recreational drug use, family history especially of malignancy and reproductive history.
5. Physical Exam: A complete (C) physical exam (including height at screening only) will be conducted at screening and at the EOT visit. A brief (B) physical exam will be conducted at the other time points.
6. Baseline Signs & Symptoms: patients will be asked about any signs and symptoms experienced within the 14 days prior to study entry. Baseline signs and symptoms will be recorded on the electronic case report form (eCRF).
7. Weight: Patient's body weight will be measured at the beginning of each cycle and drug doses for that cycle will be based on the patient's body weight.
8. Vital signs: blood pressure (BP), heart rate (HR), and temperature to be recorded in the sitting position.
9. Performance status: use Eastern Cooperative Oncology Group (ECOG) performance status criteria (Appendix 3)
10. 12-lead ECG: A single ECG will be collected on at least a 10 second strip at screening and after infusion of evorpaccept (ALX148) on C1D1, C1D8, and C3D1. No further study-mandated ECGs are needed after C3D1, except an ECG will be done at the Final study / treatment discontinuation visit. If the QTcF is prolonged (value of >500 msec), the ECG should be re-evaluated by a qualified person at the institution for confirmation. Additional ECGs should be performed as clinically indicated.

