### Secondary Objectives:

1. To determine the disease-control rate (DCR), defined as stable disease, partial response, or complete response with evorpacept (ALX148), cetuximab, and pembrolizumab using RECIST v1.1
2. To determine the duration of response (DOR) with evorpacept (ALX148), cetuximab, and pembrolizumab, defined as the time from response (partial or complete) to progression using RECIST v1.1 or death from any cause
3. To determine the progression-free survival (PFS) with evorpacept (ALX148), cetuximab, and pembrolizumab, defined as the time from enrollment to the first observation of progression using RECIST v1.1 or death from any cause
4. To determine the overall survival (OS) with evorpacept (ALX148), cetuximab, and pembrolizumab, defined as the time from enrollment to death from any cause
5. To determine the first cycle dose-limiting toxicities (DLT) of evorpacept (ALX148), cetuximab, and pembrolizumab in stage 1
6. To evaluate the safety and tolerability of evorpacept (ALX148), cetuximab, and pembrolizumab, defined and graded according to the NCI CTCAE v5.0

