### 8.1 EFFICACY ASSESSMENTS

Baseline tumor assessments should be performed  $\leq 28$  days before Cycle 1 Day 1 and assessed according to RECIST v1.1 and iRECIST (see Appendix 2). The same procedure used to assess disease sites at baseline should be used throughout the study (e.g., the same contrast protocol for CT scans or MRI scans). CT or MRI scans should include chest, abdomen, and pelvic scans; and other areas as clinically indicated. At the investigator's discretion, imaging may be repeated at any time if progressive disease is suspected. Evaluation of tumor response conforming to RECIST v1.1 and iRECIST must be documented every 9 weeks  $\pm 5$  days (no matter where the patient is in the treatment cycle). Patients in both the safety run-in and dose expansion stages will continue to receive study therapy until disease progression according to RECIST v1.1 (Appendix 2), unacceptable toxicity, death, patient or physician decision to withdraw, or pregnancy, whichever occurs first.

In all cohorts, at the time of RECIST v1.1-defined progression (i.e. iUPD), treatment is permitted to continue until the next assessment (at least 4 weeks but no longer than 8 weeks later) if the following criteria are met:

- Patient is clinically stable (An assignment of clinical stability requires that no worsening of performance status has occurred, that no clinically relevant increases in disease-related symptoms such as pain or dyspnea occur that are thought to be associated with disease progression (these symptoms are generally understood to mean a requirement for increased palliative intervention), and that no requirement for intensified management of disease-related symptoms exists, including increased

- analgesia, radiotherapy, or other palliative care.)
- Absence of tumor progression at critical anatomical sites (e.g., leptomeningeal disease) that cannot be managed by protocol-allowed medical interventions
  - Patient and investigator agree to continue treatment
  - Patient signs the Treatment Beyond Progression Informed Consent Form
  - If the subsequent scan continues to show progression, all therapy will be discontinued and the patient will be taken off study.

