If iUPD is noted, a follow-up scan should be obtained at least 4 weeks but no longer than 8 weeks later. Schedule of tumor assessments are independent of any changes to the study treatment administration schedule (e.g., dose delay) and may occur mid-cycle depending on length of cycle. If a tumor assessment must be performed early or late, subsequent assessments should be conducted according to the original schedule based on the date of first study drug administration (Cycle 1, Day 1). Confirmation of response (PR or complete response [CR]) will be done no earlier than 28 days from study entry. In the case of SD, measurements must have met the SD criteria at least once after study entry at a minimum interval not less than 6 weeks. Patients who discontinue study treatment for any reason other than disease progression will continue to undergo tumor response evaluations (approximately every 9 weeks) until progressive disease. Rising tumor markers (e.g., CEA) in the absence of radiological evidence of progression is not considered progressive disease.

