**Registration:** Site numbers are entered into the Electronic Data Capture (EDC) system when the EDC is created. Patient numbers (registration) are assigned by AGICC when the patient signs the Informed Consent Form (ICF) and the patient is entered into the EDC. Screening failures are captured in the EDC. Enrollment occurs when the Medical Monitor approves the screening documents with his/her signature.

**Concomitant Treatments:** All concomitant medications and Non-Drug Supportive Interventions should be recorded in the eCRF within 28 days prior to study entry (i.e., prior to C1D1). All concomitant medications taken during study participation will continue to be recorded continuously on the eCRF starting at the screening visit and ending 30 days after treatment discontinuation (See Section 6.6).

**Tumor Assessment:** Baseline tumor assessments should be performed  $\leq 28$  days before C1D1 and assessed according to RECIST v1.1 and iRECIST (see Appendix 2), as described in Section 8.1.

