## 9.3 POPULATION FOR ANALYSES

All analyses will be conducted using the safety-evaluable population, defined as all patients who receive any amount of study drug. Exploratory efficacy analyses will also be conducted using the response-evaluable population (see Section 12.2 for definition).

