## 9.4 STATISTICAL ANALYSES

### 9.4.1 GENERAL APPROACH

The primary analysis will be based on patient data collected through study discontinuation or at the end of study. All analyses will be conducted using the safety-evaluable population, defined as all patients who receive any amount of study drug. Exploratory efficacy analyses will also be conducted using the response-evaluable population (see Section 12.2 for definition).

Summary descriptive statistics will be calculated and presented for all primary, secondary, safety, and exploratory outcomes for all participants, and for stratifications defined by participant demographic characteristics. The demographic characteristics of the participants will be presented with descriptive statistics also. The means, medians, and 95% confidence intervals will

be calculated for continuous variables; the frequencies, estimated rates, and the exact 95% confidence intervals will be calculated for binary and categorical variables.

The safety, tolerability, and clinical activity of evorpaccept (ALX148), cetuximab, and pembrolizumab will be described and summarized, as warranted by sample size. That is, listings may be used in lieu of tables in the event of small sample size. Analysis of the primary efficacy, secondary efficacy, and exploratory endpoints will be performed as described in sections 9.4.2, 9.4.3, and 9.4.8, respectively. Safety analyses will be performed as described in section 9.4.4.

---

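### PFS and OS run from enrollment although only dosed patients are analysed and scans are counted from first dose; separately, the 6-month PFS landmark falls just before the third scan window

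*Protocol*

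**What the plan says.** Section 3 gives PFS as "defined as the time from enrollment to the first observation of progression using RECIST v1.1 or death from any cause", and OS also starts at enrollment. Section 8.2.1 fixes what enrollment means: "Enrollment occurs when the Medical Monitor approves the screening documents with his/her signature". That sign-off closes screening, so it precedes Cycle 1 Day 1 (C1D1). Its distance from C1D1 is not stated; the only bound is that screening is "to be obtained within 28 days prior to study entry" (Section 1.3, footnote 1).

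The analysis set is narrower than the enrolled set. Section 9.4.1 says: "All analyses will be conducted using the safety-evaluable population, defined as all patients who receive any amount of study drug".

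On imaging, Section 8.1 says "Evaluation of tumor response conforming to RECIST v1.1 and iRECIST must be documented every 9 weeks", with a tolerance of 5 days either way. It counts the schedule from C1D1: "subsequent assessments should be conducted according to the original schedule based on the date of first study drug administration". Extra imaging is allowed whenever progression is suspected.

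Section 9.4.3 tests PFS with a one-sided one-sample log-rank test at 0.05 against a historical 6-month PFS of 20%, with a target of 40%. It also reports a landmark estimate: "The survival probability (Kaplan-Meier survival curve) at 6 months will be calculated by the Kaplan-Meier method". It assumes 48 patients, 12 months of accrual, 6 months of further follow-up and exponential times, and states 95.6% power, an event probability of 0.82 and 39 events.

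**The concern.** Three fixed elements do not share an origin. The clock starts at sign-off, while membership of the analysis set and the scan calendar both start at first dose. Nobody who progresses or dies between sign-off and first dose can enter the analysis, so that stretch is survived by definition. A one-sample log-rank test compares observed events with those the null hazard predicts over the time each patient is followed. Time that cannot contain an event lowers the observed count relative to the expected one and pushes the test toward a positive result.

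The landmark is a separate matter of reading. An estimate taken shortly before a scheduled scan omits the progressions that scan will find, yet it would be read against 20% and 40%.

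The trial has one arm, so no concurrent control cancels either effect. At stake is a powered secondary claim about PFS, plus a small lengthening of reported OS.

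**Working it through.** **Inputs from the protocol.** N = 48; null and target 6-month PFS 20% and 40%; exponential times; accrual 12 months plus 6 months of follow-up (9.4.3); scans every 9 weeks ±5 days from C1D1 (8.1). **Assumption.** The lag from sign-off to first dose, taken as 3, 7 and 14 days. The 28-day screening window is an outer limit; because sign-off follows the screening work, lags near it are unlikely to be typical. One month is taken as 30.4375 days, so 6 months is 182.6 days.

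**1. The plan's own figures.**
- Hazards: h0 = -ln(0.2)/6 = 0.2682 per month; h1 = -ln(0.4)/6 = 0.1527 per month; ratio 0.569.
- Event probability under the target: 1 - (0.4 - 0.4³)/(12 × 0.1527) = 1 - 0.336/1.833 = 0.817; times 48 = 39.2 events.
- Power, with null variance E for the test and the exact variance under the target: 95.6%.

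All three stated figures reproduce and are not in question.

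**2. Effect of the lag on the test.** Each treated patient accrues h0 × lag of expected events with no possibility of an observed one. Over 48 patients that is 48 × 0.2682 × lag/30.4375:
- 3 days: 1.3 extra expected events
- 7 days: 3.0
- 14 days: 5.9

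For scale, the null predicts 48 × 0.940 = 45.1 events without a lag. Simulation (200,000 trials of 48 patients under the 20% null, exact event times, rejecting when (O - E)/√E is below -1.645) gives:

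| Assumed lag | Type I error | True 20% reads, at 6 months from enrollment |
|---|---|---|
| 0 days | 4.1% | 20.0% |
| 3 days | 5.7% | 20.5% |
| 7 days | about 9% | 21.3% |
| 14 days | about 17% | 22.6% |
| 28 days (outer limit) | about 45% | 25.6% |

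The last column is 0.2^((182.6 - lag)/182.6). Using (O + E)/2 as the variance gives 5.0%, 6.9%, 10% and 20% for 0, 3, 7 and 14 days, so the pattern does not depend on the form of the test.

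**3. Position of the landmark.**
- Week 18 is day 126. Week 27 is day 189, with window day 184-194.
- Six months from C1D1 is day 182.6, which is 1.4 days before the window opens. Counted from enrollment it is earlier still: day 175.6 after C1D1 with a 7-day lag.
- The last scheduled scan before the landmark is therefore week 18. If every progression waited for a scheduled scan, a true 20% would read 0.2^(126/182.6) = 32.9%, and a true 40% would read 53.1%. If half were dated when they occurred, 20% would read 26.5%; if three quarters were, 23.2%.

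**4. A landmark after the window closes.** Week 28 is day 196. The same exponential gives 0.2^(196/182.6) = 17.8% and 0.4^(196/182.6) = 37.4%. If all progression were found at day 189, the reading would be 18.9% and 38.7%. About one percentage point of delay remains, against up to 13 points at 6 months.

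**The case against.** **The historical 20% is probably delayed too.** PFS is defined by first observation of progression, and a benchmark drawn from efficacy data on third-line drugs presumably rests on observed progression as well. The documents give neither the scan schedules nor the clock starts behind it. This stands, and it limits the landmark point: a control scanned every 9 weeks would also read up to 32.9%, and the excess would vanish. With scans every 4, 6, 8 or 12 weeks, a week-24 scan comes before month 6 and a true 20% reads at most 22.8%. Which case applies cannot be settled here.

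**Not every event waits for a scan.** Deaths are dated exactly and suspected progression may be imaged at any time. This also stands, so 33% is a ceiling. A reader might infer that the landmark always misses everything after week 18; that is true only of progression found at on-schedule scans. Table 1 also marks tumor assessment in the Day 15 column, and Cycle 9 Day 15 is day 182. That column cannot be taken literally: Cycle 3 Day 15 is day 56, outside the first window of day 58-68. The 9-week rule in footnote 20 governs.

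**The benchmark may matter more.** Appendix 4 gives median PFS of 1.9, 3.2, 2.0 and 2.0 months for the active third-line arms. Under an exponential these imply 6-month PFS of 2^(-6/median) = 11%, 27%, 12.5% and 12.5%. If the truth were a 2.0-month median, a 14-day lag alone would give rejection below 0.3%. This is fair, but type I error is defined at the plan's own 20% null, and slack from a strict benchmark is no reason to keep a clock that erodes it. At the 3.2-month median the benchmark errs the other way.

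**The lag is assumed.** Correct: the sizes are conditional, although the direction is not. A reader might add that the lag is longer in Cohort A because of the biopsy. The protocol places that biopsy after eligibility is confirmed and before C1D1, but does not say whether it precedes or follows the sign-off.

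**PFS is secondary.** The futility rule and the primary test use ORR alone. This limits the consequence.

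**Conclusion.** The mismatch between the PFS/OS clock and the treated-only population is in the text, and its direction is certain. Its size depends on an unstated interval: type I error of about 6%, 9% or 17% for lags of 3, 7 or 14 days, against about 4% with none, taking the 20% as free of the same lag. The landmark point also holds, as a matter of reporting: the 6-month estimate carries scheduled-scan information only to week 18 and could read up to about 33% when the truth is 20%.

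A reader might go further and infer that scan delay by itself takes the test's type I error to around 61%, or 22% if half the events are dated at once. Those figures follow only if the historical 20% contains no detection delay, which the documents do not support. Nor does the position of week 27 drive the formal test: the log-rank uses the whole follow-up, not the value at 6 months. The change is worth making, but nothing here affects the primary endpoint or the stated power and event count.

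**What to change.** 1. Define PFS and OS from C1D1 (first dose). This matches the treated-only population and the scan anchor, and Appendix 2 already measures stable-disease duration from the start of treatment.
2. Report the Kaplan-Meier landmark at week 28, after the third scan window closes, against 17.8% (null) and 37.4% (target) from the same exponential. Moving the clock alone does not solve this, since 6 months from C1D1 still falls before day 184.
3. State that the log-rank comparison assumes the historical 20% comes from a comparable scan schedule and clock start.

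An interval-censored test is not required. Setting a hazard for the unseen time of progression against a benchmark built on observed progression would create a new mismatch.

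The cost is wording and slightly less favourable PFS and OS figures. Week 28 also lies 196 - 182.6 = 13.4 days beyond the 6-month minimum follow-up assumed in the power calculation, so the last patients need about two more weeks before the estimate is complete. No extra patients, scans or visits are needed.

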#### **9.4.4 SAFETY ANALYSES**

Safety will be assessed through summaries of adverse events. Adverse events will include changes in symptoms, changes in medical conditions, changes in vital signs, and changes in laboratory values. Additionally, separate summaries will be created which will include only serious adverse events (SAEs). When subjects experience multiple events of varying severity, the highest grade will be used in the subject-level summaries. Toxicity will be summarized and tabulated based on organ and severity.

---

#### **9.4.5 BASELINE DESCRIPTIVE STATISTICS**

The demographic characteristics of the participants will be presented with descriptive statistics. The means, medians, and 95% confidence intervals will be calculated for continuous variables; the frequencies, estimated rates, and the exact 95% confidence intervals will be calculated for binary and categorical variables.

---

#### **9.4.6 PLANNED INTERIM ANALYSES**

An interim efficacy analysis will be performed based on the first 24 evaluable patients as detailed in Section 9.4.2.

#### 9.4.7 TABULATION OF INDIVIDUAL PARTICIPANT DATA

Tabulation data sets will be created which provide a tabular listing of subject data for all domains (e.g. demographics, outcomes, adverse events, etc).

#### 9.4.8 EXPLORATORY ANALYSES

Analyses of ORR, DCR, DOR, and PFS per iRECIST compared to historical controls will be performed in a similar manner as described in Sections 9.4.2 and 9.4.3.

The change in pre- and post-treatment immune cells in the tumor microenvironment as measured by nine-color multispectral imaging will be evaluated using a paired t-test. The pre-treatment means, post-treatment means, mean difference between the pre- and post-treatment tumor infiltrating scores, and the 95% confidence intervals will be reported. A sample size of 18 achieves 81% power to detect a mean of paired differences of 5% with an estimated standard deviation of differences of 7% with a significance level (alpha) of 0.05 using a two-sided paired t-test. To account for non-evaluable biopsy specimens or patient dropout, the size of the Cohort A will be 23.

Additional exploratory analyses will be performed as sample size allows.

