### Exploratory Objective:

1. To compare the objective response rate (ORR), disease-control rate (DCR), duration of response (DOR), and progression-free survival (PFS) determined according to RECIST v1.1 to that identified by iRECIST
2. To identify immune modulation (myeloid and lymphoid) in the peripheral blood and tissue biopsies pre- and post-treatment with evorpaccept (ALX148), cetuximab, and pembrolizumab
3. To correlate immune modulation in the peripheral blood and tissue biopsies pre- and post-treatment with evorpaccept (ALX148), cetuximab, and pembrolizumab with response
4. To evaluate the relationship between PD-L1, EGFR, and CD47 tumor expression and efficacy of evorpaccept (ALX148), cetuximab, and pembrolizumab
5. To evaluate the relationship between tumor mutational burden (TMB) and efficacy of evorpaccept (ALX148), cetuximab, and pembrolizumab

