## 9 STATISTICAL CONSIDERATIONS

## 9.1 STATISTICAL HYPOTHESES

### Primary Hypothesis:

1. Evorpaccept (ALX148), cetuximab, and pembrolizumab will demonstrate improved objective response rate (ORR, per RECIST v1.1) compared to historical controls

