### Exploratory Hypotheses:

1. Evorpaccept (ALX148), cetuximab, and pembrolizumab will demonstrate improved objective response rate (ORR), disease-control rate (DCR), duration of response (DOR, and progression-free survival (PFS) per iRECIST compared to historical controls
2. After treatment with evorpaccept (ALX148), cetuximab, and pembrolizumab, there will be an enhanced immune response in the peripheral blood and tumor tissue compared to pre-treatment
3. Immune profiles in patients with an objective response to evorpaccept (ALX148), cetuximab, and pembrolizumab will show enhanced immune response in the tumor and peripheral blood compared to non-responders (by RECIST v1.1 and iRECIST)
4. Objective response rate will not correlate with pre-treatment PD-L1 tumor expression by immunohistochemistry (by RECIST v1.1 and iRECIST)
5. Objective response rate will not correlate with pre-treatment EGFR tumor expression by immunohistochemistry (by RECIST v1.1 and iRECIST)
6. Objective response rate will not correlate with pre-treatment CD47 tumor expression by immunohistochemistry (by RECIST v1.1 and iRECIST)
7. Objective response rate will be higher for patients with high tumor mutational burden (TMB, >10 mut/Mb) than for patients with low TMB (<10 mut/Mb) (by RECIST v1.1 and iRECIST)

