## 9.2 SAMPLE SIZE DETERMINATION

The sample size for stage 1 is not based on formal statistical calculations. Rather, it is based on a desire to obtain sufficient safety and tolerability information while exposing as few patients as possible to the investigational treatments.

The sample size for stage 2 has been determined as follows. The currently available third-line treatment options for MSS mCRC are regorafenib and trifluridine-tipiracil, however ORR is <5% and improvements in PFS and OS minimal, if any (Appendix 4). As previously discussed, expected response to single agent treatment with either anti-PD-1 or EGFR inhibitor in this patient population is extremely poor (Appendix 12, including linked references). Efficacy data from currently available third-line treatment options for MSS mCRC will comprise an estimation of the historical control (null hypothesis): ORR 3%, DCR 45%, and 6-month PFS probability 20%. In this study, we estimate ORR 15%, DCR 65%, and 6-month PFS probability 40%.

In paired pre- and post-treatment biopsies in patients with lung cancer and head/neck cancer treated with evorpaccept (ALX148) and pembrolizumab, mean intra-tumoral pre- and post-treatment staining with CD68, CD163, and CD8 was 9 to 13%, 11 to 17%, and 8 to 10%, respectively. Based on this data, in this study, we will assume an expected mean of the paired differences of 5% with an expected standard deviation of the paired differences of 7%.

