#### **9.4.2 ANALYSIS OF THE PRIMARY EFFICACY HYPOTHESIS & STOPPING CRITERIA**

The one-sided proportion test will be conducted for ORR against the null hypothesis that the ORR is less than or equal to 3%, with significance level of 0.05. The cumulative frequency, estimated proportion, and the exact 95% confidence intervals will be reported. A sample size of 48 achieves 87% power if the ORR is 15% using a one-sided exact test with a target significance level of 0.05. These results assume that the ORR of the historical control is 3%.

For  $\alpha = 0.025$  (1-sided) and power of 87%, MinMax design supports stopping enrollment for futility as noted if there are no responses (partial response or complete response as defined in the protocol) in first 24 subjects. Otherwise, full study enrollment will proceed as planned. Using a Simon-like 2-stage design, ORR will be determined based on the first 24 evaluable patients (including patients in both Stage 1 and Stage 2). If there are no responses (partial response or complete response as defined in the protocol) in the first 24 evaluable patients, then study enrollment will be stopped for futility. If there is at least one response (partial response or complete response as defined in the protocol) in the first 24 evaluable patients then full study enrollment will proceed as planned. If there are no responses (partial response or complete response as defined in the protocol) in the first 23 evaluable patients then enrollment will be temporarily paused to allow response evaluation of the 24th evaluable patient after up to 15 total weeks (ie 5 total cycles) of study therapy. If the 24th patient has response (partial response or complete response as defined in the protocol) then then full study enrollment will proceed as planned. If the 24th patient does not have a response (partial response or complete response as defined in the protocol) then the study will be stopped for futility. See Section 9.4.2 for statistical considerations.

---

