### 3.1 Confirming Progression

Unlike RECIST 1.1, iRECIST requires the confirmation of progression and uses the terms iUPD (unconfirmed progression) and iCPD (confirmed progression). Confirmatory scans should be performed at least 4 weeks, but no longer than 8 weeks after iUPD.

iCPD is confirmed if further increase in tumor burden, compared to the last assessment, is seen as evidenced by one or more of the following:

- Continued increase in tumor burden (from iUPD) where RECIST 1.1 definitions of progression had been met (from nadir) in target, non-target disease or new lesions
  - Progression in target disease worsens with an increase of at least 5 mm in the absolute value of the sum
  - Continued unequivocal progression in non-target disease with an increase in tumor burden
  - Increase in size of previously identified new lesion (s) (an increase of at least 5 mm in the absolute value of the sum of those considered to be target new lesions) or additional new lesions.
- RECIST 1.1 criteria are met in lesions types (target or non-target or new lesions) where progression was not previously identified, including the appearance of additional new lesions.

If iUPD is not confirmed at the next assessment, then the appropriate response will be assigned (iUPD if the criteria are still met, but no worsening, or iSD, iPR or iCR if those criteria are met compared to baseline). As can be seen in Table 5, the prior documentation of iUPD does not preclude assigning iCR, iPR, or iSD in subsequent time-point assessments or as best overall response (BOR) providing that iCPD is not documented at the next assessment after iUPD.

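### The stated iRECIST analysis tests ORR, DCR and PFS against the RECIST v1.1 null rates instead of comparing the two criteria, and those tests lean toward rejection

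*Protocol*

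**What the plan says.** Protocol Section 3, Exploratory Objective 1 (repeated in the Synopsis), asks for ORR, DCR, DOR and PFS "determined according to RECIST v1.1 to that identified by iRECIST". That is a comparison of two criteria within the same patients.

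Section 9.1, Exploratory Hypothesis 1, asks a different question. It expects the same four endpoints to be improved "per iRECIST compared to historical controls". Section 9.4.8 follows the hypothesis, not the objective: "Analyses of ORR, DCR, DOR, and PFS per iRECIST compared to historical controls will be performed in a similar manner" to Sections 9.4.2 and 9.4.3.

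Those two sections hold the tests for the RECIST v1.1 endpoints. For ORR: "The one-sided proportion test will be conducted for ORR against the null hypothesis that the ORR is less than or equal to 3" per cent, at a significance level of 0.05. DCR has a one-sided proportion test against 45%, and PFS a one-sided one-sample log-rank test against a 6-month probability of 20%. DOR has neither a null value nor a named test, and is to be compared with history only if numbers allow.

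Section 9.2 gives the only nulls in the document: "historical control (null hypothesis): ORR 3%, DCR 45%, and 6-month PFS probability 20" per cent. It takes them from currently available third-line options. The primary hypothesis, that the regimen "will demonstrate improved objective response rate (ORR, per RECIST v1.1) compared to historical controls", uses the same source.

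On how the criteria differ, Appendix 2, item 3.1, says that "the prior documentation of iUPD does not preclude assigning iCR, iPR, or iSD in subsequent time-point assessments or as best overall response (BOR", provided progression is not confirmed at the next assessment.

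**The concern.** Two things do not fit together.

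First, the objective and the analysis are different comparisons. One is RECIST v1.1 against iRECIST in the same patients. The other is iRECIST against outside rates. No analysis of the first kind is stated.

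Second, the outside rates do not match the endpoint. One set of nulls serves both criteria, and iRECIST can only leave a patient's result unchanged or move it upward. A one-sided upper test of an iRECIST rate against a RECIST v1.1 null therefore counts the change of criteria as apparent benefit. At stake is an exploratory statement that DCR, ORR or PFS is improved per iRECIST, part or all of which could come from the scoring rule.

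**Working it through.** **Inputs**

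- Section 9.4.2: ORR null 3%, alternative 15%, N = 48, one-sided 0.05, stated power 87%.
- Section 9.4.3: DCR null 45%, alternative 65%, N = 48, one-sided 0.05, stated power 87%.
- Section 9.4.3: PFS at 6 months 20% against 40%, N = 48, 12 months' accrual plus 6 months' follow-up, stated power 95.6%, event probability 0.82, 39 events.
- Share of patients reclassified by iRECIST: not in the protocol. Assumed here as k = 1, 2 or 3 of 48.

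**Step 1: reproduce the plan's figures.** For a proportion, reject when X ≥ r, where r is the smallest count with P(X ≥ r | n = 48, p0) ≤ 0.05 under the exact binomial.

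- ORR: r = 5. P(X ≥ 5 | 0.03) = 0.0143, and power P(X ≥ 5 | 0.15) = 0.866.
- DCR: r = 28. P(X ≥ 28 | 0.45) = 0.0438, and power P(X ≥ 28 | 0.65) = 0.868.
- PFS: one-sample log-rank with exponential survival and the null variance. Power 0.956, event probability 0.817, 48 × 0.817 = 39.2 events.

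All three agree with the protocol. The tests are sound for rates measured on the same scale as the nulls.

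**Step 2: direction of the difference.** Under RECIST v1.1 the first qualifying progression counts. Under iRECIST a first, unconfirmed progression can be followed by iSD, iPR or iCR, and that later category can be the best overall response. The footnote to Table 5 in Appendix 2 says that without pseudoprogression the response categories of the two systems coincide. So the iRECIST response and disease-control rates are equal to or higher than the RECIST v1.1 rates. This can occur in practice: Section 4.1.2 allows conditional treatment past a first progression until a further assessment 4 to 8 weeks later.

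**Step 3: effect on the test.** Suppose the regimen equals historical control by RECIST v1.1, and iRECIST raises the underlying rate by k/48. The rejection chance is P(X ≥ r | 48, p0 + k/48).

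| k of 48 | DCR by iRECIST | P(X ≥ 28) | ORR by iRECIST | P(X ≥ 5) |
|---|---|---|---|---|
| 0 | 45.0% | 4.4% | 3.0% | 1.4% |
| 1 | 47.1% | 7.8% | 5.1% | 9.6% |
| 2 | 49.2% | 13.0% | 7.2% | 25.9% |
| 3 | 51.3% | 20.1% | 9.3% | 46.1% |

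The ORR column needs the reclassified patients to become responders; the DCR column needs only stable disease or better. The 5% level is passed once the iRECIST rate under no RECIST v1.1 benefit exceeds 45.5% for DCR or 4.2% for ORR. In patients these are (0.455 − 0.45) × 48 ≈ 0.2 and (0.042 − 0.03) × 48 ≈ 0.6, both below one.

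**Step 4: are the nulls iRECIST rates?** The protocol does not say which criteria the historical trials used. Its reference list dates the four third-line trials 2013, 2015, 2015 and 2018, and the iRECIST guideline 2017. Three of the four came first. That the nulls are not iRECIST rates is therefore an inference. That identical nulls are used for both criteria is in the text.

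**Step 5: what the matching analysis would give.** Every patient is scored by both systems (Section 8.1), so the proportion reclassified can be estimated directly with an exact 95% interval: 1/48 = 2.1% (0.1% to 11.1%), 2/48 = 4.2% (0.5% to 14.3%), 3/48 = 6.3% (1.3% to 17.2%).

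**The case against.** The strongest reply is that little rests on this. The endpoints are labelled exploratory, the primary and secondary efficacy endpoints use RECIST v1.1, and no decision in the protocol depends on an iRECIST p-value. That stands, and it limits the weight of the point.

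A reader might infer that objective 1 goes wholly unanswered. The protocol does not support that. Section 9.4.1 promises descriptive statistics for all primary, secondary and exploratory outcomes, with exact intervals for binary ones, so both sets of estimates would appear. A detailed paired method could also sit in an SAP. What remains is that the protocol states an analysis, and it is a different one from its objective.

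A reader might also take the table as the error rate for a regimen that does nothing. It is not. The number reclassified is assumed. Appendix 2 attributes the difference to immune infiltration, which would itself be a drug effect, so an inert regimen might produce few reclassifications. Early deaths and non-evaluable patients cannot be upgraded, and an upgrade needs a later scan showing stable disease or better.

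Nor do the documents support a figure for PFS. They do not fix the event date for iRECIST progression, and PFS events include deaths, which no criteria change can move. For DOR, no one-sided test is specified at all.

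**Conclusion.** The point holds as an inconsistency in the protocol with a known direction of bias. Objective 1 compares two criteria; Hypothesis 1 and Section 9.4.8 test iRECIST ORR, DCR and PFS against nulls shared with RECIST v1.1. Because iRECIST results are equal or better, those tests lean toward rejection.

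The size is a sensitivity illustration. It assumes no benefit by RECIST v1.1, N = 48, the exact tests of Sections 9.4.2 and 9.4.3, and an assumed 1 to 3 patients moving upward. On those terms the nominal 5% is exceeded from the first patient for both DCR and ORR. No PFS or DOR figure is claimed. The mismatch between objective and analysis rests on the text alone; the mismatch of the nulls rests partly on the inference from reference dates.

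**What to change.** In Section 9.1, Exploratory Hypothesis 1, and the first sentence of Section 9.4.8, make the within-patient comparison of RECIST v1.1 with iRECIST the stated analysis:

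- cross-tabulate best overall response by the two criteria;
- report the number and proportion of patients reclassified, with an exact 95% confidence interval;
- give paired differences in ORR and DCR with 95% confidence intervals;
- show PFS and DOR by both criteria side by side.

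Keep the formal tests against 3%, 45% and 20% for the RECIST v1.1 endpoints only. If historical context for iRECIST is wanted, present it descriptively, without a test.

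The cost is wording in two places, with no new scans, data or patients. What is lost is an exploratory test that has no matching comparator.
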